## **11.6 Finance and Insurance**

The sponsor will purchase insurance for subjects participating in this study in accordance with local regulations and minimum requirements. The terms of the insurance will be kept in the study binder.

## 12 Protocol Amendment History

| Version | Date       | Description of Change                     |
|---------|------------|-------------------------------------------|
| V1.0    | 02/28/2020 | N/A, this is a new protocol               |
| V1.1    | 24/04/2020 | See Protocol Amendment Record for details |
| V2.0    | 11/13/2020 | See Protocol Amendment Record for details |
| V2.1    | 2020/12/14 | See Protocol Amendment Record for details |

## 14 Appendix

### Appendix 1: Pancreatic Enzyme Monitoring and Management Procedures for Patients without Symptoms of Pancreatitis 1, 2

[figure not shown]

1. Symptomatic refers mainly to abdominal pain associated with pancreatitis, and severe nausea, vomiting, and other symptoms can also be considered as related symptoms by the investigator.
2. If at any time the investigator believes that a subject has symptoms of acute pancreatitis, regardless of whether based on L/A test results, the investigator should consult a specialist for evaluation, management, assessment of the cause of pancreatitis, discontinuation of dosing and notification of the sponsor.
3. Either or both of serum lipase and serum amylase can be used as the evaluation criteria.
4. The optimal time for abdominal imaging is when elevated pancreatic enzymes are just found. If judged safe by the investigator or imaging physician, it is best to use enhanced

## Appendix 2: CKD-EPI formula (eGFR estimation formula)

Estimated by CKD-EPI formula:  $eGFR = a \times [(serum\ creatinine\ (\mu\text{ mol/L})/b)]^c \times (0.993)^{age}$ ;

| Sex    | A Value | B-value | C-value                          |                                |
|--------|---------|---------|----------------------------------|--------------------------------|
|        |         |         | Serum creatinine $\leq$ 0.7mg/dl | Serum creatinine $>$ 0.7 mg/dl |
| Female | 144     | 0.7     | -0.329                           | -1.209                         |
| Male   | 141     | 0.9     | -0.411                           | -1.209                         |

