### **3.2 Phase Ib/II Study Design**

#### **3.2.1 Overall Study Design**

This study has enrolled 36 overweight or obese subjects (Cohort 1, Cohort 2, and Cohort 3) with weight change of less than 5% controlled by diet and exercise for at least 12 weeks. All subjects were safe and well tolerated (see Section 1.3. 2 and 1.3. 3 for details). Based on the current PK data of subjects in Cohorts 1-3 showing that the plasma concentration in Chinese overweight/obese population is lower than the plasma concentration prespecified in the study, Cohort 4 and Cohort 5 will be further explored, with 12 subjects in each group, and an estimated total of 24 subjects will be added based on the Chinese PK data of IBI362. The entire trial period consisted of a 3-week screening period, a 12-to 16-week double-blind treatment period, and an 8-week follow-up period after the last dose.

The double-blind treatment phase was divided into five cohorts, Cohort 1 (n=12), Cohort 2 (n=12), Cohort 3 (n=12), Cohort 4 (n=12), and Cohort 5 (n=12), and subjects in each cohort were randomized in a 2: 1 ratio to IBI362 treatment (n=8) and placebo (n=4). The SC dosing regimens of IBI362 or placebo in Cohort 1, Cohort 2, Cohort 3, Cohort 4, and Cohort 5 are described as follows:

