#### 4.1 Inclusion Criteria

Subjects met all of the following criteria to be included in the study:

1. Age 18 ~ 75 years (both inclusive), male or female;
2. Obese:  $BMI \geq 28.0 \text{ kg/m}^2$ ; Or overweight:  $24 \leq BMI < 28.0 \text{ kg/m}^2$  with at least one of the following manifestations: i. Strong appetite, unbearable hunger before meal, and more food intake per meal; ii. Patients with one or more of pre-diabetes (impaired fasting glucose and/or impaired glucose tolerance), hypertension, dyslipidemia (see Annex 4 for reference standards), and fatty liver (within 6 months prior to screening); iii. Combined weight-bearing joint pain; iv. Obesity-induced dyspnea or obstructive sleep apnea syndrome;
3. Controlled by diet and exercise alone for at least 12 weeks at screening, with body weight change of less than 5%;
4. Able to understand the procedures and methods of this study, willing to strictly comply with the clinical trial protocol to complete this trial, and voluntarily sign the informed consent form.

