4. Any laboratory test indicator meeting the following criteria (if there is a clear reason for retest at screening, it can be retested within one week, and the investigator should record the reason for retest):
- 1) Serum calcitonin  $\geq 15$  ng/L at screening;
  - 2) Alanine aminotransferase  $\geq 2.0 \times \text{ULN}$  and/or aspartate aminotransferase  $\geq 2.0 \times \text{ULN}$  and/or total bilirubin  $\geq 1.0 \times \text{ULN}$  and/or alkaline phosphatase  $\geq 2.0 \times \text{ULN}$  at screening;
  - 3) Glomerular filtration rate eGFR  $< 60$  mL/min/1.73 m^2 at screening, as estimated by the CKD-EPI equation (see Appendix 2);
  - 4) Abnormal thyroid function (FT3, FT4, or TSH) at screening;
  - 5) Fasting triglycerides  $\geq 5.64$  mmol/L (500 mg/dl) at screening, if the subject is on lipid-modifying therapy, the drug dose must be stable for 30 days prior to screening;
  - 6) Blood amylase or lipase  $> 2.0 \times \text{ULN}$  at screening;
  - 7) International normalized ratio (INR) of prothrombin time greater than the upper limit of normal at screening.
5. Heart rate  $< 50$  beats/min or  $> 90$  beats/min on 12-lead ECG at screening;

6. Subjects with the following clinically significant 12-lead electrocardiograms (ECGs) abnormalities at screening: second or third degree atrioventricular block without a pacemaker, long QT syndrome or QTcF > 450ms (see Appendix 3 for calculation formula), PR interval < 120ms or PR interval > 220ms, QRS > 120ms, left or right bundle branch block, pre-excitation syndrome, or serious arrhythmia requiring treatment;
7. Pregnant or lactating females, males or females of childbearing potential not willing to use contraception throughout the study;
8. Blood donation and/or blood loss  $\geq$  400 mL or bone marrow donation within 3 months prior to screening, or presence of hemoglobinopathy, hemolytic anemia, sickle cell anemia, or hemoglobin < 110g/L (male) or < 100g/L (female);
9. The subject has any other factors that may affect the efficacy or safety evaluation of this study, and is not suitable for participation in this study in the opinion of the investigator.

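### Appendix 2 divides creatinine in µmol/L by a constant on the mg/dL scale, so the eGFR <60 exclusion, applied as printed, rejects essentially every candidate

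*Protocol*

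**What the plan says.** Protocol Appendix 2 gives eGFR as a × (creatinine / b)^c × 0.993^age. The creatinine term is printed as "serum\ creatinine\ (\mu\text{ mol/L})/b", so the value to enter is in µmol/L. The constants a, b and the first c are listed as "Female | 144 | 0.7 | -0.329" and "Male | 141 | 0.9 | -0.411". The second c is -1.209 for both sexes. Which c applies depends on two column headers, "Serum creatinine $\leq$ 0.7mg/dl" and "Serum creatinine $>$ 0.7 mg/dl", and these serve both rows of the table.

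The formula decides eligibility. Section 4.2, criterion 4, item 3) excludes a subject whose eGFR is below 60 mL/min/1.73 m² "at screening, as estimated by the CKD-EPI equation (see Appendix 2"), and the Protocol Summary repeats the criterion. Section 4 allows no deviation from the eligibility criteria. The protocol contains no creatinine conversion and no other version of the formula.

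**The concern.** The ratio creatinine / b makes sense only if both are in the same unit. The unit of b is not labelled, but the table switches exponent at 0.7 mg/dL, which is numerically the female b, so b is on the mg/dL scale while the numerator is in µmol/L. The numerator is then too large by the conversion factor, and because c is negative, eGFR comes out too low.

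There is a second fault in the same table. A two-branch formula of this form is continuous only where creatinine equals b, since the ratio is then 1 and c drops out. For women the cut-off equals b. For men the cut-off is 0.7 and b is 0.9, so the function has a step.

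What is at stake is a mandatory entry criterion in a multicentre study with competitive enrolment (section 8.6.1) and 24 subjects still planned for Cohorts 4 and 5 (section 3.2.1). A site that follows the text can enrol nobody. A site that uses another calculator departs from the text, and the protocol does not fix which calculation it then uses.

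**Working it through.** The protocol gives no worked eGFR value to reproduce, so the formula was evaluated directly.

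**Inputs from the protocol**
- Appendix 2: women a = 144, b = 0.7, c = -0.329 or -1.209; men a = 141, b = 0.9, c = -0.411 or -1.209; age factor 0.993^age; c switches at 0.7 mg/dL.
- Section 4.1: "Age 18 ~ 75 years (both inclusive), male or female".
- Section 4.2: exclusion if eGFR <60.

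**Assumptions not in the protocol**
- 1 mg/dL creatinine = 88.4 µmol/L.
- Illustrative creatinine values, 20 to 129 µmol/L overall.

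**Size of the unit error.** Entering µmol/L over a mg/dL constant multiplies eGFR by 88.4^c:
- 88.4^-0.329 = 0.229 (women, lower branch)
- 88.4^-0.411 = 0.158 (men, lower branch)
- 88.4^-1.209 = 0.0044 (upper branch, both sexes)

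**Worked cases**
- Man, 40 years, 80 µmol/L (80/88.4 = 0.905 mg/dL, upper branch). As printed: 141 × (80/0.9)^-1.209 × 0.993^40 = 0.47. In mg/dL: 141 × (0.905/0.9)^-1.209 × 0.993^40 = 105.8.
- Woman, 40 years, 60 µmol/L (60/88.4 = 0.679 mg/dL, lower branch). As printed: 144 × (60/0.7)^-0.329 × 0.993^40 = 25.1. In mg/dL: 144 × (0.679/0.7)^-0.329 × 0.993^40 = 109.8.
- Woman, 18 years, 35 µmol/L. As printed: 144 × (35/0.7)^-0.329 × 0.993^18 = 35.0. In mg/dL: 153.1.

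**Can any candidate pass as printed?** Over both sexes, ages 18 to 75 and 20 to 129 µmol/L, the highest result is about 42 (woman, 18 years, 20 µmol/L). Above 0.7 mg/dL (about 62 µmol/L) every result is below 1. Setting the printed formula equal to 60 and solving gives the highest creatinine that would pass: b × (60 / (a × 0.993^age))^(1/c).

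| Age | Women, µmol/L | Men, µmol/L |
|---|---|---|
| 18 | 6.8 | 5.3 |
| 40 | 4.3 | 3.6 |
| 75 | 2.0 | 2.0 |

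With mg/dL in the numerator, the exclusion at age 40 begins above about 101 µmol/L (1.15 mg/dL) in women and 128 µmol/L (1.45 mg/dL) in men.

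**Male cut-off.** The two male branches at 0.7 mg/dL differ by (0.7/0.9)^(-1.209 + 0.411) = (0.7/0.9)^-0.798 = 1.222, an upward step of 22% as creatinine rises. At age 40, on the mg/dL reading, eGFR goes from 118.7 at 61 µmol/L to 143.9 at 62 µmol/L. Only men between 0.7 and 0.9 mg/dL are affected. The lowest value there is at 0.9 mg/dL and age 75, 141 × 0.993^75 ≈ 83, so no decision at 60 changes.

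**Converted constants.** 0.7 × 88.4 = 61.9 µmol/L and 0.9 × 88.4 = 79.6 µmol/L.

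**The case against.** The strongest reply is that nothing has gone wrong in practice. Section 3.2.1 records that "This study has enrolled 36 overweight or obese subjects", which could hardly have happened under literal use. The criterion names the CKD-EPI equation, a user must have creatinine in mg/dL anyway to choose c, and an eGFR of 0.47 in an ambulatory volunteer would be noticed at once. The unit error can only lower eGFR, so it cannot admit someone with poor renal function. eGFR is used only at screening and enters no endpoint or analysis. The male step changes no eligibility decision, and non-uniformity between sites is a conjecture.

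Much of this stands. There is no evidence of wrong exclusions, no trial result depends on eGFR, the direction is conservative, and the male step is a matter of correctness only. That sites differed is a possibility and not a finding.

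It does not rescue the text. The enrolments suggest that eligibility was decided by a calculation other than the one written, and the protocol does not say which. The criterion points to Appendix 2, so the appendix is the operative definition. The conflicting units are explicit and legible, with nothing redacted. A shared header could in principle be a flattened table cell, but that would bear only on the male cut-off.

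**Conclusion.** The concern holds. As printed, Appendix 2 contradicts itself on units, and the exclusion that relies on it would reject every eligible age at any realistic creatinine. The printed eGFR is about 23% of the mg/dL value (women, lower branch), 16% (men, lower branch) or 0.4% (upper branch). The shared cut-off for men is a separate, smaller error with no effect at 60.

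The conclusion rests on b being in mg/dL, which follows from the cut-off in the same table, and on the factor 88.4. The example creatinine values are illustrative, but the result is not sensitive to them: passing as printed would need at most 6.8 µmol/L. This is an error in the wording of a mandatory rule and should be corrected before Cohorts 4 and 5 are screened. It is not evidence that subjects were wrongly excluded.

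**What to change.** Use one unit throughout Appendix 2. Either print creatinine in mg/dL in the formula and leave b at 0.7 and 0.9, or keep µmol/L, set b to 61.9 (women) and 79.6 (men), and convert the cut-offs for c as well. In the same edit, give each sex a cut-off for c equal to its own b, so that both functions are continuous. The <60 threshold itself is untouched.

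Send the corrected formula to all sites, ask which calculation they have been using, and recheck any eGFR that was computed from Appendix 2. The cost is one appendix correction and a site letter.

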### **Appendix 3: QTcF Calculation Formula**

QTc Fridericia formula:  $QTcF = QT / (RR ^ {0.33})$

#### **Appendix 4: Dyslipidemia Reference Standards**

Refer to Guidelines for Prevention and Treatment of Dyslipidemia in Chinese Adults  
(2016 Revision)

## **Appendix 5: Oral Glucose Tolerance Test (OGTT) Methods**

1. Beginning at 7-9 a.m., subjects were orally administered 75 g of anhydrous glucose dissolved in 300 mL of water after fasting (8-10 h), or 82.5 g if 1 molecule of water was used. Children are given 1.75 g per kilogram of body weight, not to exceed 75 g. Sugar water was taken within 5 minutes.
2. Blood samples were taken from forearm before and 2 hours after taking glucose from the first mouth of glucose.
3. During the course of the study, the subjects did not drink tea or coffee, did not smoke, did not do strenuous exercise, but were not absolutely bed-ridden.
4. Blood samples should be submitted as soon as possible.
5. The daily carbohydrate intake shall not be less than 150 g within 3 days prior to the test.
6. The drugs that may affect OGTT, such as contraceptives, diuretics or phenytoin sodium, were stopped for 3 ~ 7 days before the test.

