| Serum calcitonin                                          | X                             |                               |    |    |    |    |    |    |    |     |     |     |     |     |     |     |     |     |     |     |     |     |     |     |     |     |     | X                |     |                  | X |
| Blood pregnancy test                         | X                             |                               |    |    |    |    | X  |    |    |     |     |     | X   |     |     |     |     |     |     | X   |     |     |     |     |     |     |     | X                |     |                  | X |
| Thyroid function                             | X                             |                               |    |    |    |    |    |    |    |     |     |     |     |     |     |     |     |     |     |     |     |     |     |     |     |     |     | X                |     |                  |   |

| Study Phases and Procedures                                          | Screening Period  | Double-Blind Treatment Period |    |    |    |    |    |    |    |     |     |     |     |     |     |     |     |     |     |     |     |     |     |     |     |     |     | Safety Follow-up |     | Early Withdrawal |   |   |
|----------------------------------------------------------------------|-------------------------------|-------------------------------|----|----|----|----|----|----|----|-----|-----|-----|-----|-----|-----|-----|-----|-----|-----|-----|-----|-----|-----|-----|-----|-----|-----|------------------|-----|------------------|---|---|
| Study Visits                                                         | V1                            | V2                            | V3 | V4 | V5 | V6 | V7 | V8 | V9 | V10 | V11 | V12 | V13 | V14 | V15 | V16 | V17 | V18 | V19 | V20 | V21 | V22 | V23 | V24 | V25 | V26 | V27 | V28              | V29 | V30              |   |   |
| Study duration (weeks)                                               | -3 ~ 0                        | 1                             | 2  | 3  | 4  |    | 5  |    | 6  | 7   | 8   |     | 9   |     | 10  | 11  | 12  |     |     | 13  |     | 14  | 15  | 16  |     |     |     | 17               | 20  | 24               |   |   |

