**Notes:**

1. If the examination at screening is more than 5 days away from the day of administration, it should be confirmed again within 5 days before administration, including vital signs, physical examination, hematology, blood biochemistry, lipid profile, coagulation function, urinalysis, myocardial enzymes, serum amylase and lipase, thyroid function, serum calcitonin, ECG and pregnancy test.
2. Window for vital signs: to be completed within 1 hour prior to dosing (except for non-dosing visits).
3. Physical examination: in the physical examination of skin and mucosa after administration, attention should be paid to the observation of abnormalities at the injection site. In addition to the examination time points listed in the table, the local skin and mucous membrane at the injection site should be observed for abnormalities immediately ( $\pm 2$  min), 20 min ( $\pm 5$  min), 40 min ( $\pm 5$  min) and 60 min ( $\pm 5$  min) after administration, including but not limited to skin erythema/redness, swelling, pain/tenderness, congestion/hemorrhage, etc.
4. Body weight: The subjects were required to take off their coat after urination and fasting at each measurement. The same subject used the same scale each time and avoided strenuous exercise before measurement.
5. Waist circumference: (1) standing position, relaxed shoulders and abdomen, smooth breathing, feet 25-30cm apart; (2) The horizontal position of measurement: the midpoint of the

line between the anterior superior iliac spine and the inferior margin of the 12th costal line on the midaxillary line; (3) Use a tape ruler around the abdomen in the above-mentioned horizontal position, with the tape ruler closely adhering to the skin, but not strangling the skin; (4) The measurement should not be made consciously with the abdomen closed or lifted, and the measurement should be taken at the calm end of expiration, with the waist circumference in cm to the nearest mm (e.g., 89.3 cm).

6. Hip circumference: (1) The subject stands naturally, with shoulders relaxed, arms naturally drooping and moderately open, legs together, legs evenly loaded, hips relaxed, and eyes ahead; (2) Horizontal positions measured: symphysis pubis anteriorly and greater trochanter of femur posteriorly; (3) Generally equivalent to the most protruding part of the buttock; (4) Wrap the buttocks horizontally with a tape ruler and record the values.
7. [6.2.1](#)Laboratory tests include: (refer to Section 6.2. 1)

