14. 4For subjects with fasting blood glucose of 6.1-7.0 mmol/L at screening, venous blood glucose 2 hours after OGTT glucose load should be collected for confirmation. Refer to Appendix 5 for OGTT method.
15. Dual-energy X-ray (DEXA) and abdominal MRI are recommended to be performed at sites where conditions permit. DEXA method determination: The subject lies on the examination table, uses the DEXA standard mode, the scanning frame moves from the head side to the foot side, and scans. The scanning conditions were voltage ( $76 \pm 3$ ) KV and current 0.15 mA, tube voltage of two X-rays was 38 V and 70 KV, respectively, the scanning particle range was 197 cmx60 ca, the width was fixed at 60 cm, the scanning time was about 5 min, and the radiation absorber was 0.002 mGy. At the end of the measurement, DEXA device automatically recorded the fat weight of the whole body, waist and buttocks and other parameters, and calculated the waist-buttock fat ratio: waist fat weight (g)/buttock fat weight (g). PLODIGY dual-energy X-ray absorptiometry (Lunar, GE Company, USA) was recommended as the equipment used.
16. Immunogenicity sampling points: Week 1 (within 1h before dosing on Day1), Week 5 (within 1h before dosing on Day29), Week 9 (within 1h before dosing on Day57), Week 13 (within 1h before dosing on Day85), Week 17 (168 h  $\pm$  12 h after dosing on Day106) and Week 24 Follow-up Visit. If a subject withdraws early, whenever possible, 1 immunogenicity sample will be collected at the early withdrawal visit. 5 mL of whole blood will be collected at each blood collection point. Detailed procedures will be described in the central laboratory manual.
17. 55Refer to Table 5-1 and Table 5-2 for PK/PD sampling points.
18. In this study, fasting blood collection was required to be fasted for at least 8 hours, and the drug was administered after fasting blood collection and then fed.

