#### **4.3 Restrictions during the Study**

- Subjects should not donate blood during their participation in this study and within 8 weeks after the last dose;
- Men or women of childbearing potential must use contraception during the study and for 8 weeks after the last dose.
- Not allowed to participate in other clinical trials;
- During the trial, the original diet, exercise and lifestyle were maintained steadily, and binge eating and strenuous exercise were taboo;
- Alcohol consumption was prohibited during the trial.

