##### **5.4.2 Childbearing age**

Female subjects of childbearing potential who are sexually active with a non-sterilized male partner, and non-sterile male subjects who are sexually active with a female partner of childbearing potential must use at least 1 acceptable effective method of contraception from screening until 8 weeks after the last dose and should discuss the discontinuation of contraception with a responsible physician after that time point.

Women were considered postmenopausal after 12 months of menopause without an alternative medical cause. The requirements according to age are as follows:

- Women  $\geq 50$  years of age are considered postmenopausal if they have been amenorrheic for 12 months or more after cessation of exogenous hormone therapy and their luteinizing hormone and follicle-stimulating hormone levels are in the accepted postmenopausal range.
- Women  $< 50$  years of age were considered postmenopausal if they had been amenorrheic for 12 months or more after cessation of all exogenous hormonal therapy, had been oophorectomized with the last menses occurring  $> 1$  year earlier with radiation therapy, had been amenorrheic with the last menses occurring  $> 1$  year earlier with chemotherapy, or had been surgically sterilized (bilateral oophorectomy or hysterectomy).

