#### **6.2.6 Pregnancy test**

A blood pregnancy test is required for women of childbearing potential before enrollment. If the pregnancy test is positive, the subject is not eligible/must be discontinued from the study. If pregnancy is suspected during the study, it should be repeated.

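### Appendix 5 tells sites to stop contraceptives for 3 to 7 days before the screening OGTT, while Section 5.4.2 requires effective contraception from screening and nothing reconciles the two

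*Protocol*

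**What the plan says.** The OGTT is done at screening only, in subjects whose screening fasting glucose is 6.1 to 7.0 mmol/L. The notes to the visit schedules (Table 2 note 15, Table 4 note 14, Table 6 note 14) send the site to the appendix for the procedure: "venous blood glucose 2 hours after OGTT glucose load should be collected for confirmation. Refer to Appendix 5 for OGTT method". Item 6 of Appendix 5 then reads: "The drugs that may affect OGTT, such as contraceptives, diuretics or phenytoin sodium, were stopped for 3 ~ 7 days before the test".

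The contraception rules are elsewhere. Under Section 5.4.2, sexually active women of childbearing potential and non-sterile men with partners of childbearing potential "must use at least 1 acceptable effective method of contraception from screening until 8 weeks after the last dose". Section 4.3 says: "Men or women of childbearing potential must use contraception during the study and for 8 weeks after the last dose". Exclusion criterion 7 in Section 4.2 bars anyone of childbearing potential who is unwilling to use contraception throughout.

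On pregnancy testing, Section 6.2.6 states: "A blood pregnancy test is required for women of childbearing potential before enrollment". Note 1 to Tables 2, 4 and 6 adds that if screening was more than 5 days before dosing, a list of examinations is confirmed again within 5 days before dosing. That list ends with "serum amylase and lipase, thyroid function, serum calcitonin, ECG and pregnancy test". In all three tables the pregnancy-test row has entries at screening and then at D29, with none on D1.

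**The concern.** Item 6 is an explicit instruction to stop, and it names contraceptives. It covers days on which Section 5.4.2 already requires an effective method. No text exempts the OGTT days, asks for a substitute method, or says when the stopped method is restarted or can be relied on again.

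The stake is subject safety. The protocol keeps pregnant women out (Section 4.2), withdraws those who become pregnant (Section 4.5.3) and requires a report within 24 hours (Section 7.6). It should not also direct a pause in contraception just before first exposure to an investigational drug, especially when a pregnancy that is not clinically suspected could go undetected through the first dose level.

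**Working it through.** There is no planned statistical figure to reproduce. The check compares the texts and counts days and doses.

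**Inputs**
- Stop: 3 to 7 days before the OGTT (Appendix 5, item 6).
- Screening: D-21 to D-1, followed by D1 with no Day 0 (Tables 2, 4 and 6).
- Dosing: weekly from D1 (same tables). The first dose level is 2.5 mg in Cohort 4 and 3.0 mg in Cohort 5 (Section 3.2.1).
- Pregnancy tests: screening, repeated within 5 days before dosing if screening is older than that (note 1); then D29 with a window of ±2 days.
- Enrolment: 36 of 60 subjects already in the study. For Cohorts 4 and 5, "an estimated total of 24 subjects will be added based on the Chinese PK data of IBI362".

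**Does the stop fall where Section 5.4.2 applies?** The OGTT is triggered by a fasting glucose measured at screening. A stop made because of that result begins after screening has started, so the contraception duty is already in force.

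**Position of the stop relative to the first dose** (method resumed after the test)
- Latest case, OGTT on D-1: a 3-day stop covers D-4, D-3 and D-2; a 7-day stop covers D-8 to D-2.
- Earliest case, stop beginning on D-21: a 3-day stop covers D-21 to D-19, with the OGTT on D-18; a 7-day stop covers D-21 to D-15, with the OGTT on D-14.

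**Position of the last required pre-dose pregnancy test** (D-5 to D-1)
- Latest case: the test can fall during the stop (for example on D-5 within a 7-day stop) or at most 1 day after its last day (D-2 to D-1). A conception from those days could well be missed.
- Earliest case: the test falls 19 - 5 = 14 to 19 - 1 = 18 days after a 3-day stop, or 15 - 5 = 10 to 15 - 1 = 14 days after a 7-day stop. Detection is then more likely.

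**Exposure before the next scheduled test**
- Doses before D29: D1, D8, D15 and D22, so 4 doses.
- Cohort 4: 4 × 2.5 mg = 10 mg. Cohort 5: 4 × 3.0 mg = 12 mg.
- Interval from the last required pre-dose test to D29: from D-1, 1 + 28 = 29 days; from D-5, 5 + 28 = 33 days.
- With the ±2-day window: D-1 to D27 = 1 + 26 = 27 days; D-5 to D31 = 5 + 30 = 35 days.

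During that interval a further test is done only if pregnancy is suspected (Section 6.2.6).

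**Who can still be reached:** 60 - 36 = 24 subjects, the planned size of Cohorts 4 and 5 together.

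**The case against.** The strongest reply is that there is no true contradiction. Item 6 concerns drugs, so it reaches contraceptive drugs and not contraception as such. Section 5.4.2 asks for an effective method without requiring a hormonal one, so a barrier or other non-drug method satisfies both. The duty appears in three places (Sections 4.2, 4.3 and 5.4.2), and a site that leaves a woman unprotected breaches all of them. Appendix 5 also reads as general OGTT text: item 1 gives a dose for children in a trial of adults aged 18 to 75. The harm needs a long chain of conditions, and the dose totals and day counts describe the schedule without giving a probability of pregnancy.

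Much of this stands. The protocol does not permit going without contraception, the two rules can be met together, and the affected group is likely to be tiny. The closeness to first dosing is greatest only when the OGTT is late in screening. The limited sensitivity of a very early pregnancy test applies to any contraceptive lapse and is not a separate fault of the schedule.

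It does not remove the point. Appendix 5 is the text the schedules tell staff to follow when preparing an OGTT, and it says stop without saying switch. The generic origin of the appendix may explain how the sentence got in, but sites are still directed to use it.

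**Conclusion.** The concern holds as a minor safety and consistency point. Item 6 directs a 3 to 7 day stop of contraceptives within the period in which Section 5.4.2 requires an effective method, and no text connects the two. In the worst timing the stop ends on D-2, the last required pregnancy test is uninformative about it, and four doses are given before the D29 test.

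This assumes an OGTT late in screening, a woman whose only method is hormonal, a site that applies item 6 without switching her, and no clinical suspicion of pregnancy before D29. The documents do not give the number of such women. It is probably very small and, for future enrolment, lies within the 24 subjects of Cohorts 4 and 5. No estimate, test or conclusion of the trial is affected. The change is optional but worthwhile.

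**What to change.** Reword item 6 of Appendix 5 in one of two ways:
- state that contraceptives are not stopped for the OGTT; or
- state that a hormonal method may be stopped only if an effective non-hormonal method is used from the first day of the stop until the hormonal method is effective again, with a cross-reference to Section 5.4.2.

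This is one sentence, with no new visit, test or procedure. The cost is that a few OGTTs may be read while the woman is on hormonal contraception, or that she needs a temporary alternative method.
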